### Safety assessment

The safety set (SS) population, which will include randomized subjects who have made at least one visit, will be used for safety analysis. The frequency of adverse events and incidence of abnormalities in laboratory tests before and after treatment will be compared for the two groups using a chi-squared test. Any possible causal relationship between the test drug and the abnormality will be detected using an appropriate statistical model

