### Measurement items and time points of data collection

Relevant examinations will be performed and patient data will be collected at 2 weeks before baseline, at baseline, at 2 weeks post baseline and every 4 weeks from 4 to 16 weeks during treatment. Items to be measured and the time points of data collection can be found in Table 1.

**Table 1 T1:** Measurement items and point of data capture

	**Screening**	**Baseline**	**Treatment**				
	**Visit 1**	**Visit 2**	**Visit 3**	**Visit 4**	**Visit 5**	**Visit 6**	**Visit 7**
**Items**	**−2 weeks**	**0 weeks**	**2 weeks**	**4 weeks**	**8 weeks**	**12 weeks**	**16 weeks**
Informed consent form	X						
Inclusion/exclusion criteria	X						
Demographic information	X						
Medical/drug use history	X						
Concomitant disease and treatment	X						
General physical examination	X						
Combined medication	X	X	X	X	X	X	X
Vital signs	X	X	X	X	X	X	X
TCM symptom	X	X	X	X	X	X	X
Urine protein test	X	X	X	X	X	X	X
Routine urine test	X	X	X	X	X	X	X
Renal function (SCR, BUN, GFR) Serum albumin	X	X	X				X
Routine blood test	X	X					X
Stool routine test and fecal occult blood test	X	X					X
Liver function (ALT/AST/GGT/TBIL/ALB)	X	X					X
Blood electrolytes	X	X	X				X
Blood coagulation (TT/APTT/PT/FIB)	X	X					X
Blood glucose	X	X	X	X	X	X	X
Glycosylated hemoglobin	X	X			X		
Electrocardiogram (EGG)	X	X					X
Adverse events	X	X	X	X	X	X	X
Randomization		X					
Drug distribution	X	X	X	X	X	X	
Drug recycling		X	X	X	X	X	X
Drug count		X	X	X	X	X	X
Research conclusion							X

X: Have indicators tested in the specific time period. ALB, serum albumin; ALT, alanine aminotransferase; APTT, activated partial thromboplastin time; AST, aspartate aminotransferase; BUN, blood urea nitrogen; FIB, fibrinogen; GFR, glomerular filtration rate; GGT, gamma-glutamyl transpeptidase; PT, prothrombin time; SCR, serum creatinine; TBIL, total bilirubin; TCM, traditional Chinese medicine; TT, thrombin time.

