### Sample size calculation

This is an exploratory phase II clinical study designed to provide evidence and a scientific rationale for advancing the treatment regimen into a phase III confirmatory study. The planned sample size is 80, with 40 in each treatment group.

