### Efficacy assessment

All primary analyses for this study will strictly follow the intention-to-treat (ITT) principle. The full analysis set (FAS) population, which will include randomized subjects who have received treatment at least once, will be used for primary efficacy outcomes analysis. In addition, a per-protocol analysis will be performed on the secondary outcomes. The per-protocol set (PPS) population will be restricted to patients who are compliant with the treatment protocol and have a completed CRF. Good compliance indicates the drug actually taken equals 80 to 120 percent of the required dosage. Missing values will be replaced using the last observation carried forward (LOCF) method.

Continuous variables will be described as mean ± standard deviation, and dichotomous data will be reported as percentages. A two-tailed test will be applied. Statistical significance will be defined as *P* <0.05 and 95% confidence interval will be calculated. Heterogeneity between groups will be tested at baseline.

The main analysis will be a comparison between the two groups concerning the proportion of patients achieving different levels of recovery (FR, GR, MR or NR) in terms of TCM symptoms and clinical biomarkers using the Wilcoxon rank sum test. In addition, the ORR will be compared between the two arms using the center-stratified Cochran-Mantel-Haenszel (CMH) method. For secondary outcomes, all continuous data will be analyzed via analysis of covariance adjusted for clinical center and baseline. Analyses of binary data will be based on logistic regression models.

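### The safety set is defined by attendance at a visit rather than by exposure to study drug, so on neither reading of 'visit' does it hold all treated patients and only those

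*Protocol article*

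**What the plan says.** Under Safety assessment, the protocol article fixes the population for safety: "The safety set (SS) population, which will include randomized subjects who have made at least one visit, will be used for safety analysis". The sentence sets no dosing condition and does not say which visit counts. AE frequency and laboratory abnormalities in this population "will be compared for the two groups using a chi-squared test".

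Under Efficacy assessment, the full analysis set (FAS) is made up of "randomized subjects who have received treatment at least once". The exposure condition therefore appears on the efficacy set and not on the safety set.

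Under Measurement items and time points of data collection, examinations take place "at 2 weeks before baseline, at baseline, at 2 weeks post baseline and every 4 weeks from 4 to 16 weeks during treatment". Table 1 in that section numbers screening as Visit 1, baseline as Visit 2 and week 2 as Visit 3. It marks randomization at Visit 2 only.

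**The concern.** A safety set should hold everyone exposed to study drug, and nobody else, so that an AE rate is a rate among people who could have reacted to the drug. A visit condition does not achieve this. It can admit patients who were never exposed, or exclude patients who were exposed and then left. The second is the more troubling, because an early reaction can be the reason for leaving.

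Safety is part of the stated objective, and the abstract names a lower frequency of AEs among the hoped-for benefits. Under Sample size calculation, "The planned sample size is 80, with 40 in each treatment group". With arms of that size, one or two patients visibly move a rate.

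**Working it through.** The article gives no AE rate, no never-dosed count and no early-loss count, so there is no figure of the plan's own to reproduce. The check compares the definitions and then does denominator arithmetic on assumed counts.

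**Inputs**
- From the article: n = 40 per arm; randomization at Visit 2; first post-baseline visit is Visit 3 (week 2).
- Assumed: an AE rate of 20% among dosed patients, and 1 to 4 patients per arm who are never dosed or lost early.

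**Step 1: who is in each set**

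| Randomized patient | FAS | Safety set, any visit counts | Safety set, post-baseline visit needed |
|---|---|---|---|
| Dosed, attends week 2 or later | in | in | in |
| Dosed, never returns | in | in | out |
| Never dosed, never returns | out | in | out |
| Never dosed, attends week 2 or later | out | in | in |

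On the literal reading every randomized patient qualifies, because each attended screening and baseline beforehand. On the post-baseline reading a dosed patient can be in the FAS but not in the safety set. Neither column matches exposure. The two consequences are alternatives and cannot occur together.

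**Step 2: literal reading**

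Let k of 40 be never dosed, a of those k have an AE recorded, and p be the rate among the dosed. The reported rate is [p(40 − k) + a]/40. With p = 20% and a = 0:
- k = 1: 0.20 × 39/40 = 19.5%
- k = 2: 0.20 × 38/40 = 19.0%
- k = 4: 0.20 × 36/40 = 18.0%

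The relative understatement is k/40: 2.5%, 5% and 10%. It is not automatic. Table 1 records AEs from screening onwards, so a never-dosed patient can have one. With k = 1 and a = 1 the rate is (7.8 + 1)/40 = 22.0%. The rate falls only if a/k is below p.

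**Step 3: post-baseline reading**

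Let E of 40 dosed patients have an AE, m leave before Visit 3, and x of those m have an AE. The reported rate is (E − x)/(40 − m), against a true E/40. With E = 8 (20%) and m = 2:
- x = 2: 6/38 = 15.8%
- x = 1: 7/38 = 18.4%
- x = 0: 8/38 = 21.1%

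The rate falls only if x/m exceeds E/40.

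In the worst case every early leaver had an AE. With 4 AE patients among those who return:
- m = 1: 4/39 = 10.3% against 5/40 = 12.5%
- m = 2: 4/38 = 10.5% against 6/40 = 15.0%
- m = 4: 4/36 = 11.1% against 8/40 = 20.0%

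The gap runs from about 2 to about 9 percentage points.

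**The case against.** The best defence is that little will come of this. Table 1 marks drug distribution at the randomization visit, so few patients should be randomized and never dosed. The tablets are blinded, so never-dosing should be similar in both arms. If k is equal in the two arms and the never-dosed have no AEs, both rates scale by (40 − k)/40 and the risk ratio does not change. The study calls itself exploratory, and no sample size or decision rule depends on the safety set. All of this stands for the literal reading, and it limits the size of the point. It does not help the post-baseline reading, where early leaving may follow a reaction to one treatment and so differ between arms. That reading, however, is not stated in the text; it is only one that the wording leaves open.

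It could also be said that an analysis plan, due before data lock, would settle this. But the article does not leave the population open. It states a rule, and the rule is the wrong one.

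Two stronger inferences are tempting and are not supported:
- **That AE rates are biased downwards on either reading.** Steps 2 and 3 show that each can go up or down.
- **That the chi-squared test will produce false safety signals.** For 4/40 against 0/40 the uncorrected test gives P = 0.040 and Fisher's exact test 0.116, but the continuity-corrected test gives 0.124. The article does not say which form of chi-squared is meant and gives no AE rates. An exact test for sparse cells is ordinary analysis-plan detail.

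**Conclusion.** The point holds as a wrong stated rule. The safety set lacks an exposure condition, the qualifying visit is undefined, and nothing else in the article repairs either.

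Read literally, the condition excludes nobody and the effect is probably small: 20% becomes 19.5% with one never-dosed, AE-free patient in an arm of 40. Read as post-baseline, the distortion can be larger, up to about 9 percentage points in the extreme case of four early leavers who all had AEs. The direction depends on whether the wrongly included or excluded patients had AEs.

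The fault follows from the text alone. The sizes rest entirely on assumed rates and counts. If nearly all randomized patients take a dose and return at week 2, the numerical effect is close to nil. No claim is made here about the choice of test.

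**What to change.** Redefine the safety set as all randomized patients who received at least one dose of study drug, with no visit requirement, using the same exposure wording as the FAS. The sentence should also say which drug counts as study drug, because Table 1 marks drug distribution at Visit 1, before randomization, as well as at later visits.

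The cost is one sentence in the protocol or the analysis plan. Enrolment was still open when the article was written and the analysis plan is due only before data lock, so the change can be made in time. It needs no new scheduled assessment, since Table 1 already lists drug counts from Visit 2. For patients who never return, whether a dose was taken will have to be established by other contact and recorded. The choice between chi-squared and exact tests can be left to the analysis plan.

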### Other criteria

#### Concomitant treatments and forbidden drugs

•Use of any other Chinese medicine or western therapy like ACEIs or ARBs to relieve symptoms of diabetic nephropathy ought to be strictly prohibited.

•Use of medication to control other conditions of the patients, such as anticoagulatory or lipid-lowering drugs, is allowed.

•Details of any additional drug or therapy taken must be recorded in the case report form (CRF). These include drug name, dose and treatment duration.

Early suspension or termination of the trial will occur in the following situations:

•Occurrence of serious adverse events, flawed protocol or significant deviation in implementation.

•Funding or management problems.

•The administrative authorities decide to terminate the study.

Patients will be withdrawn or be rejected for further participation on the grounds below:

•Voluntarily quitting.

•Use of forbidden medication or treatment during the trial that might affect analysis of results.

•Early termination of the process based on the investigator’s judgment (in the case of misdiagnosis, development of severe complications, and so on.).

•Failure to keep the patient blinded, or deblinding in case of emergency.

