### Interventions

Participants randomized to the treatment group will be administered SYKFT 2.4 g three times daily plus irbesartan 0.15 g once daily for 16 weeks. Those in the control group will receive SYKFT placebo 2.4 g three times daily in addition to irbesartan 0.15 g once daily for 16 weeks. Both groups will receive behavioral intervention and health education such as diet instructions. All test drugs, that is SYKFT, the placebo and irbesartan (trade name: Anbowei in Chinese pinyin) are manufactured by Tianjin Tongrentang Pharmaceuticals.

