### Reporting of adverse events

Adverse events (AEs) will be recorded in medical diagnostic terminology. Detailed symptoms, time of occurrence, duration, severity, possible causal relationships, actions taken, results and other relevant information will be reported. In the case of an adverse event, researchers must fill out a serious adverse event (SAE) form and notify both the institutional review board (IRB) and the regulatory authorities within 24 hours.

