### Randomization and allocation concealment

A total of 80 patients will be randomly assigned in a ratio of 1:1 to either the SI or the PI group using a computer-generated random number sequence. To guarantee rigorous methodology, center-stratified randomization and central coordination will be initiated. The central randomization system will assign a unique code to each newly included participant, who will then be administered the corresponding treatment regimen.

An expert statistician of the Tianjin Institute of Clinical Evaluation and a staff member from the sponsoring organization will act as the coder, and they will be shielded from patient recruitment. The trial management board will be responsible for keeping the blinding codes and other information confidential.

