## Abbreviations

ACEIs: Angiotensin-converting enzyme inhibitors; AEs: Adverse events; ALB: Serum albumin; ALT: Alanine aminotransferase; APTT: Activated partial thromboplastin time; ARBs: Angiotensin receptor blockers; AST: Aspartate aminotransferase; BUN: Blood urea nitrogen; CRF: Case report form; DN: Diabetic nephropathy; ECG: Electrocardiogram; EI: Efficacy indicator; FAS: Full analysis set; FIB: Fibrinogen; FR: Full recovery; GFR: Glomerular filtration rate; GGT: Gamma-glutamyl transpeptidase; GR: Good recovery; IRB: Institutional review board; ITT: Intention-to-treat; LOCF: Last observation carried forward; MR: Modest recovery; NR: No recovery; ORR: Overall recovery rate; PI: Placebo and irbesartan; PPS: Per-protocol set; PT: Prothrombin time; RCT: Randomized controlled trial; SAE: Serious adverse event; SCR: Serum creatinine; SI: SYKFT and irbesartan; SOP: Standard operating procedure; SS: Safety set; SYKFT: Shenyan Kangfu tablet; TBIL: Total bilirubin; TCM: Traditional Chinese medicine; TT: Thrombin time; UACR: Urinary albumin-to-creatinine ratio; UAER: Urinary albumin excretion rate

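### The safety set's visit condition is met by every randomised patient, so anyone never dosed counts in the adverse-event denominator (minor)

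*Protocol article*

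**What the plan says.** The Safety assessment section of the protocol article sets the safety population: "The safety set (SS) population, which will include randomized subjects who have made at least one visit, will be used for safety analysis". It sets no dosing condition and does not say that the visit must follow baseline or treatment. In this set, AE frequency and laboratory abnormalities are compared between the two groups with a chi-squared test.

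The Efficacy assessment section defines the full analysis set differently, as a population "which will include randomized subjects who have received treatment at least once".

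The section on measurement items and time points has data collected "at 2 weeks before baseline, at baseline, at 2 weeks post baseline and every 4 weeks from 4 to 16 weeks during treatment". In its Table 1, screening is Visit 1 (two weeks before baseline), baseline is Visit 2, and randomisation is marked once, at Visit 2. The Randomization and allocation concealment section has each new participant given a code, "who will then be administered the corresponding treatment regimen".

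**The concern.** A safety set normally holds the people who were exposed, because an AE rate is read as the risk among those who took the treatment. Here the only condition beyond randomisation is a visit, and a patient cannot be randomised under this schedule without having attended one. The condition does no work, and the safety set becomes everyone randomised. The article applies an exposure condition to efficacy but leaves it out for safety, where exposure matters more.

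Safety is part of the stated question: the Objectives section asks whether the SYKFT regimen is superior in both efficacy and safety, and the abstract lists fewer AEs among the hoped-for benefits. At stake is whether the reported AE rates describe treated patients or are slightly diluted by patients who took nothing.

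**Working it through.** The plan states no figure to reproduce here. The check is first logical, then a bound on the size.

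**1. Who is in the set.**
- Condition: randomised, and at least one visit (Safety assessment).
- Randomisation takes place at Visit 2, after screening at Visit 1 (Table 1).
- So each randomised patient has attended Visits 1 and 2 by the time of randomisation. Safety set = all randomised, planned at 80, or 40 per arm (Sample size calculation).
- Allocated treatment follows randomisation, so a patient can be randomised and not dosed. That patient is outside the full analysis set but inside the safety set.

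**2. The other possible reading.** Suppose a post-baseline visit was meant. The first is Visit 3, at two weeks. A patient who took the drug, had a reaction and stopped attending before week 2 would then leave the safety set. That reading is also faulty, in the direction of losing harm.

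**3. Size of the dilution.** Let k be the number undosed in an arm of 40 and x the number of dosed patients with an AE. Assume that no undosed patient has an AE.
- Rate as written: x/40. Rate among dosed: x/(40 − k).
- Ratio: (40 − k)/40, a relative reduction of k/40.
- k = 1: 1/40 = 2.5%. k = 2: 2/40 = 5.0%. k = 0: no reduction.

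The article gives neither x nor k, so the values below are assumed.

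| x | k | As written | Dosed only | Difference (points) |
|---|---|---|---|---|
| 4 | 1 | 4/40 = 10.0% | 4/39 = 10.3% | 0.3 |
| 8 | 1 | 8/40 = 20.0% | 8/39 = 20.5% | 0.5 |
| 12 | 1 | 12/40 = 30.0% | 12/39 = 30.8% | 0.8 |
| 4 | 2 | 4/40 = 10.0% | 4/38 = 10.5% | 0.5 |
| 8 | 2 | 8/40 = 20.0% | 8/38 = 21.1% | 1.1 |
| 12 | 2 | 12/40 = 30.0% | 12/38 = 31.6% | 1.6 |

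**4. Why these are upper bounds.** The planned comparison is of AEs in general, not of drug-related ones, and Table 1 records AEs at every visit including screening and baseline. An undosed patient can therefore have a recorded AE. With x = 8, k = 1 and an AE in that undosed patient, the rate as written is 9/40 = 22.5% against 8/39 = 20.5% among the dosed, so it rises instead of falling.

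**5. Effect on the comparison.** If k is the same in both arms and undosed patients have no AE, the ratio of the two rates does not change. For 12 v 4 patients with an AE and k = 1 in each arm, the ratio is 3 either way; the difference is 30.0% − 10.0% = 20.0 points as written and (12 − 4)/39 = 20.5 points among the dosed. On assumed true rates of 30% v 10% and four undosed per arm, power at two-sided 0.05 (normal approximation) is 56.6% among dosed patients and 55.5% in the set as written.

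**The case against.** The strongest reply is that nothing follows in practice. Table 1 marks drug distribution at the same visit as randomisation, so undosed patients should be very few, and with none the effect is nil. Both inputs to the size are assumed. A set wider than the full analysis set loses no events. The article also promises a detailed statistical analysis plan before data locking, where set definitions can be tightened, and the visit condition may be shorthand for a post-baseline visit.

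Most of this stands as a limit on importance. It does not rescue the definition. The article states the rule; it does not leave it open. As stated, the rule excludes nobody, and the shorthand reading fails in its own way (step 2).

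A reader might infer that the AE comparison between the arms is biased. The documents do not support that: allocation is 1:1, participants and clinicians are masked, and nothing suggests that failure to start treatment would differ by arm. A reader might also take 2.5% per undosed patient as the actual loss; it is a maximum, reached only if undosed patients have no AE.

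A last objection concerns the remedy. Limiting the set to takers of SYKFT or placebo would be too narrow. The trial compares regimens that both contain irbesartan, and the Interventions section lists "All test drugs, that is SYKFT, the placebo and irbesartan" together. A randomised patient who took only the trial irbesartan has been exposed to part of the regimen and belongs in the safety analysis. This objection stands, and the fix allows for it.

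**Conclusion.** The point holds, as a minor one. The safety set as written has no exposure condition and equals all randomised patients. The consequence is bounded by a relative reduction of 1/40 = 2.5% in an arm's AE rate for each undosed patient. The bound assumes 40 per arm and no AE among the undosed. The effect disappears if all are dosed, and neither a between-arm bias nor a material loss of power is shown.

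A reader might want to add the Reporting of adverse events section, which reads "In the case of an adverse event, researchers must fill out a serious adverse event (SAE) form and notify both the institutional review board", so that taken literally any AE triggers the serious-event form. That does not enlarge this point. The name of the form and the separate mention of serious events among the grounds for stopping the trial show a missing word; the literal reading over-reports and hides nothing, and no planned analysis depends on it.

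**What to change.** Replace the definition with: the safety set comprises randomised subjects who took at least one dose of any trial medication (SYKFT, placebo or trial irbesartan) after randomisation, whether or not they return for a later visit.

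Each part has a purpose. The dosing condition restores exposure as the criterion. Naming all three products keeps patients who took only irbesartan. The words after randomisation are needed because Table 1 marks drug distribution already at Visit 1. The last clause keeps dosed patients who drop out before week 2.

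The cost is one sentence in the statistical analysis plan before data locking. No new data collection is needed, since Table 1 already schedules drug distribution, return and counts. Because counts are made only at visits, the plan should also say how a patient who never returns is classified; keeping that patient in the set unless it is known that no dose was taken is the cautious default.

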### Objectives

This clinical trial aims to assess whether Shenyan Kangfu tablets combined with irbesartan (SI regimen) is superior to a placebo combined with irbesartan (PI regimen) in efficacy and safety for DN patients with qi-yin deficiency syndrome.

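### The safety section fixes a chi-squared test as the only between-arm comparison of adverse events and promises a model that finds causality; at 40 per arm, risk differences with intervals should lead instead

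*Protocol article*

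**What the plan says.** Safety assessment defines the population: "The safety set (SS) population, which will include randomized subjects who have made at least one visit, will be used for safety analysis". For both adverse events and abnormal laboratory results, the section then says that their occurrence "will be compared for the two groups using a chi-squared test". It ends with this sentence: "Any possible causal relationship between the test drug and the abnormality will be detected using an appropriate statistical model". It names no effect estimate, no interval and no method for sparse tables.

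The general testing conventions appear only under Efficacy assessment: "A two-tailed test will be applied", followed by "Statistical significance will be defined as *P* <0.05 and 95% confidence interval will be calculated".

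On size, Sample size calculation says: "The planned sample size is 80, with 40 in each treatment group". It calls the trial an exploratory phase II study meant to support a phase III study. Safety is part of the aim, since Objectives asks whether the SYKFT regimen "is superior to a placebo combined with irbesartan (PI regimen) in efficacy and safety".

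Individual events are also documented. Reporting of adverse events says: "Detailed symptoms, time of occurrence, duration, severity, possible causal relationships, actions taken, results and other relevant information will be reported". The Other criteria section lists serious adverse events among the grounds for early suspension or termination of the trial.

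**The concern.** The one between-arm method that the article fixes for safety suits larger counts than most adverse event terms will produce at 40 per arm. It can mislead in two directions. On sparse tables the uncorrected chi-squared P value is too small, so it can declare an imbalance that an exact test would not. A non-significant P value, on the other hand, leaves large excesses of harm open, and without an interval the reader cannot see that.

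The final sentence adds a second problem. In a randomised trial the difference between arms is itself the causal comparison. A further model fitted to an abnormality cannot establish causality beyond that, and promising that it will invites a claim the data cannot carry.

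Safety is part of the objective, and the results are to inform the step to phase III, so the form of the safety summary matters.

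**Working it through.** **Inputs**
- 40 per arm, 80 in total (Sample size calculation). Full, balanced arms are assumed.
- Two-tailed P<0.05 (Efficacy assessment), taken here as the general convention because the safety section states no threshold.
- Pearson chi-squared test (Safety assessment). No continuity correction is mentioned, so none is applied.
- Event counts and true rates are illustrative assumptions.

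The planned 80 cannot be reproduced, because the article gives no effect size, event rate or power for it.

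**When tables are sparse.** With equal arms and m affected patients in total, the expected count in each event cell is m × 40/80 = m/2. This is below 5 whenever m is below 10, that is, below 12.5% of the 80 patients.

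**The test on sparse tables.** For a v b affected patients, chi-squared = 80 × [a(40-b) - b(40-a)]² / [40 × 40 × (a+b) × (80-a-b)].
- 3 v 0: 80 × 120² / (1600 × 3 × 77) = 3.117, P=0.077. Fisher: 2 × C(40,3)/C(80,3) = 2 × 9,880/82,160 = 0.241.
- 4 v 0: 80 × 160² / (1600 × 4 × 76) = 4.211, P=0.040. Fisher: 2 × C(40,4)/C(80,4) = 2 × 91,390/1,581,580 = 0.116.
- 6 v 1: 80 × 200² / (1600 × 7 × 73) = 3.914, P=0.048. Fisher: 2 × [C(40,6) × 40 + C(40,7)]/C(80,7) = 2 × 172,178,760/3,176,716,400 = 0.108.

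The smallest expected counts in these tables are 1.5, 2.0 and 3.5. For 4 v 0 and 6 v 1 the conclusion at 0.05 depends on which test is used. Against zero control events, Pearson first reaches significance at 4 and Fisher at 6 (P=0.026).

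**What a non-significant result leaves open.** The Newcombe interval combines the Wilson limits of the two arms.
- 3/40 has Wilson limits 0.0258 and 0.1986; 0/40 has limits 0 and 0.0876. The difference is 0.075.
- Lower limit: 0.075 - √[(0.075-0.0258)² + 0.0876²] = -0.025.
- Upper limit: 0.075 + √[(0.1986-0.075)² + 0²] = 0.199.
- So 3 v 0 gives an excess of 7.5 points, interval -2.5 to +19.9.
- 6 v 3 gives P=0.288 and, by the same method, an interval of -7.2 to +22.4 points.
- An event not seen in 40 patients can still have a true rate of up to 1 - 0.025^(1/40) = 8.8%.

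**Power of the planned test**, by enumerating both binomials at 40 per arm: 5% v 10% gives about 15%, 10% v 20% about 25%, and 5% v 15% about 35%.

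**The case against.** The strongest reply has four parts.

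*The interval may already be planned.* The P<0.05 threshold and the 95% interval stand in the same sentence under Efficacy assessment. If one applies to safety, so does the other. This stands in part: the placement is ambiguous, and the article cannot be said to exclude intervals for safety. The safety section nevertheless names only the test.

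*Adverse events are not judged by P values alone.* A reader might infer that they are, and that 3 v 0 could never be noticed. The documents do not support this. Severity and possible causality are recorded event by event, and serious events can stop the trial. Lack of significance at 3 v 0 also depends on full, balanced arms: 3/30 v 0/40 gives P=0.041. Nor does significance require zero control events, as 6 v 1 shows.

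*No rule treats non-significance as safety.* A reader might infer that a non-significant comparison would pass as proof of safety. The article says no such thing. Its aim is superiority in safety, which a non-significant comparison would fail to support. The risk is one of misreading.

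*The rest is detail for the analysis plan, and low power is normal.* Low power for uncommon events is expected in an 80-patient exploratory trial and is not an error. Tables by event term and the naming of a model can be left to the detailed plan that the article promises before data lock. Nothing says the model will be chosen after the data are seen. But the chi-squared test and the causality sentence are stated, not omitted, and a plan that followed them would inherit both.

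**Conclusion.** The point holds in a limited form. The article fixes, as its only between-arm safety comparison, a test that is unreliable for any event with fewer than 10 affected patients in total. At 4 v 0 and 6 v 1 it gives P values of 0.040 and 0.048 where Fisher gives 0.116 and 0.108. When the test is not significant it says little about harm: at 3 v 0 an excess of nearly 20 points is not excluded. The sentence on a model that finds causality promises something a between-group model cannot deliver.

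This rests on 40 analysed patients per arm, the uncorrected Pearson statistic, a two-tailed 0.05 level borrowed from the efficacy section, and illustrative counts. It is a correction that should be made, at low cost. It does not show that the trial would miss harm altogether or that it is too small for its exploratory purpose.

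**What to change.** In Safety assessment:
- Make the main safety comparison the number of patients with at least one event in each arm, with the risk difference and its 95% score-type (Newcombe) interval. Do the same for laboratory abnormalities.
- Where a P value is kept for a sparse table, use Fisher's exact test. It and the Newcombe interval can disagree near the 5% boundary, so say that the interval leads.
- State that a non-significant difference will not be interpreted as evidence of safety.
- Delete the sentence on the model that detects causality. Rely on the randomised difference between arms, together with the case-level causality assessment already recorded under Reporting of adverse events. That section does not say whether the assessment is made blind, so it should not be described as blinded unless this is confirmed.

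The cost is table programming, with no new data. The intervals will be wide, so the safety statement will be less favourable than a row of non-significant P values. The change can be made in the analysis plan before data lock. It would not make 3 v 0 significant, since the interval still includes zero, but it would show how much excess risk remains possible.
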